#### Planned Analyses

Demographic, educational, and bullying variables will be compared between the intervention and control groups at baseline using parametric tests, as appropriate. Multi-level mixed model analyses (three levels: school, classroom, and student) will be performed to assess the effect of treatment group (intervention vs. control group) on each outcome variable, while controlling for school socio-economic status, primary vs. secondary school, sex, and age. Additional sensitivity analyses will be performed in the group of students with SEN, where we expect to detect a similar direction of the effects, but with a larger magnitude. In the intervention group, additional analyses will test the potential effect of covariates on the effect size of the intervention, including intensity of the intervention, concomitant activities, primary vs. secondary school, bullying rates at baseline, rural vs. urban environment, and proportion of students with SEN, among others.

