## Abstract

**Introduction:** Bullying is a major preventable risk factor for mental disorders. Available evidence suggests school-based interventions reduce bullying prevalence rates. This study aims to test the efficacy of a web-enabled, school-based, multicomponent anti-bullying intervention to prevent school bullying and to assess its effects on mental health and quality of life.

**Methods and analysis:** Cluster randomized controlled trial conducted in 20 publicly funded primary and secondary schools in Madrid, Spain. Schools are randomly allocated to either the intervention arm (*n* = 10) or conventional practices arm (*n* = 10). The web-enabled intervention (LINKlusive) lasts ~12 weeks and consists of three main components: (i) an online training program for teachers and parents, (ii) a web-guided educational program for students, focusing on promoting respect for diversity, empathy, and social skill development, and (iii) a web-guided, teacher-delivered, targeted intervention program for bullying situations identified based on peer-support strategies and individual intervention for those involved (i.e., bullying victims and perpetrators). The primary objective is to compare differences between peer-reported bullying victimization in the intervention and control arms at the end of the intervention. Secondary outcome measures are additional measures of bullying victimization and perpetration, mental health symptoms, self-esteem, and quality of life. A follow-up assessment is conducted 1 year after the end of the intervention. Treatment effects will be tested using multilevel mixed models, adjusting for school-, classroom-, and student-related covariates. Considering the increased bullying rates in children with special educational needs, a specific subgroup analysis will test the efficacy of the intervention on bullying prevalence, mental health, and quality of life in this particularly vulnerable population.

**Ethics and Dissemination:** The Deontology Commission of the School of Psychology, Universidad Complutense in Madrid, Spain reviewed the study protocol and granted ethical approval on 21st January 2019. The results of the trial will be disseminated in relevant peer-reviewed journals and at conferences in the field.

**Trial Registration Number:** ISRCTN15719015.

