### School Recruitment

Figure 1 shows the flowchart for the selection of schools. Schools were selected from among publicly funded primary and secondary schools enrolling youth with SEN in mainstream classrooms in the Madrid region (*n* = 1,882). Inclusion criteria were as follows: (i) at least one previous assessment of bullying with Sociescuela in the past three years, (ii) peer-reported bullying victimization rates of at least 5% in the latest available assessment with Sociescuela, (iii) only one assessment of bullying prevalence using Sociescuela within the past 3 years (in order to have a previous measure of bullying victimization rates, but minimize previous exposure to the tool), and (iv) for primary schools, presence of specific resources for children with neurodevelopmental disorders (i.e., specific classrooms). The latter criterion was used to enrich the sample for children with neurodevelopmental conditions and accounts for the fact that primary schools in the Madrid region are increasingly incorporating so-called “neurodevelopmental disorder classrooms” or “ASD classrooms.” Therefore, students with SEN due to ASD and other neurodevelopmental conditions mainstreamed in regular schools have been preferentially assigned to schools that have such resources in the past few years. These classrooms, which enroll a maximum of 5 students per class, are usually staffed by a teacher specializing in therapeutic pedagogics or speech-language therapy and a social integration technician. Students with SEN enrolled in these classrooms spend between one- and two-thirds of the time with their peer group in their regular classroom and receive complementary pedagogic and social support through specific activities in the specialized support classroom during the remaining school hours. They also receive support to facilitate integration into the regular classroom as well as during unstructured activities such as recess.

This selection process yielded a final sample size of *n* = 29 schools (*n* = 12 primary and *n* = 17 secondary schools).

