### Study Procedures

Pupils in both groups complete all bullying (i.e., peer- and self-reported measures) and self-reported mental health and quality of life assessments on the web-based platform (www.sociescuela.es) at baseline (January 2019), study endpoint (May-June 2019), and one year after the endpoint (initially expected in May-June 2020) in both treatment groups using tablets (see Figure 1). Due to the impact of the COVID-19 pandemic in Spain, the 1-year follow-up assessment has been postponed until the 2020-2021 school year. The intervention in the experimental group took place between February and May 2019.

Teachers are available in the classroom during assessments for technical questions or clarification. For children with SEN who have comprehension difficulties, class teachers may also supervise data collection, and questionnaires and assessment methods may be adapted as required (e.g., use of visual support strategies for children with autism).

In the experimental group, additional information is collected from families and teachers through the online platform to monitor the use of designated training content. Teachers also report on the degree of completion of the school-based educational program, adherence to intervention recommendations in identified bullying cases, and their satisfaction with the program.

In experimental schools, researchers held two meetings with teaching staff, one before initiation of the intervention to explain the study procedures and present the online platform, and another visit after completion of the intervention to collect feedback. Researchers were also available by phone or e-mail for technical requests or questions regarding delivery of targeted intervention plans in particular situations.

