### Measures and Instruments

The main outcome measure of the trial is peer-reported bullying victimization (i.e., at least two peer nominations on the Sociescuela victimization subscale, see below for further details). The study also assesses the following outcome measures: peer-reported bullying perpetration, self-reported victimization and bullying perpetration, mental health symptoms (e.g., internalizing and externalizing symptoms, psychotic-like experiences), self-esteem, and quality of life (see Table 1 for a summary of the variables assessed and the instruments used in the study).

**Table 1 T1:** Variables and instruments used in the LINKlusive study.

**Variable**	**Assessment method**	**Instrument**
Peer-reported bullying victimization and perpetration	Peer-report, social network analysis within the classroom	Sociescuela (46)
Self-reported bullying victimization and perpetration	Self-report, questionnaire	*Ad hoc* questionnaire [adapted from (68)]
General psychopathology, internalizing and externalizing psychopathology	Self-report, questionnaire	Strengths and Difficulties Questionnaire and corresponding subscales (70)
Psychotic-like experiences	Self-report, questionnaire	Community Assessment of Psychic Experiences (CAPE-15) (81, 82)
Self-esteem	Self-report, questionnaire	Rosenberg self-esteem scale (83)
Quality of life	Self-report, questionnaire	KIDSCREEN-10 (86)

*Students completed all assessments through an online platform using tablets. Demographic variables were collected through an ad hoc questionnaire. Teachers also completed questionnaires regarding students with special educational needs, concomitant anti-bullying interventions conducted in schools, and adherence to the LINKlusive intervention components in the intervention group*.

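### The primary model does not adjust for baseline victimization, although it was measured in both arms; with 10 schools per arm this gives up precision and leaves chance imbalance in starting prevalence unadjusted.

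*Protocol article*

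**What the plan says.** The Abstract sets the primary comparison: "The primary objective is to compare differences between peer-reported bullying victimization in the intervention and control arms at the end of the intervention". Measures and Instruments makes the outcome binary: "at least two peer nominations on the Sociescuela victimization subscale".

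Planned Analyses gives one model for all outcomes: "Multi-level mixed model analyses (three levels: school, classroom, and student", fitted "while controlling for school socio-economic status, primary vs. secondary school, sex, and age". It names no measurement-occasion level, group-by-time term or change score, so baseline does not enter by another route.

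Baseline bullying appears twice elsewhere in that section. It is among the variables compared between arms at baseline, and it is a candidate moderator in a further analysis: "In the intervention group, additional analyses will test the potential effect of covariates on the effect size of the intervention". Neither use adjusts the comparison between arms.

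The data exist. Study Procedures has pupils in both groups complete the bullying and mental health measures "at baseline (January 2019), study endpoint (May-June 2019), and one year after the endpoint". Trial Status says that all 20 schools had a baseline assessment. School Recruitment also required one earlier Sociescuela assessment, "in order to have a previous measure of bullying victimization rates".

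**The concern.** The same measure taken about four months earlier is a natural covariate for the endpoint, and here it is already collected. Randomization of 10 schools per arm can leave the arms with clearly different starting prevalence. To the extent that prevalence persists from January to May–June, such a gap carries into the treatment estimate unless the model accounts for it.

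Two things are at stake. The first is precision, in a trial with few clusters and a rare binary outcome whose authors already name a floor effect as a limitation. The second is prespecification. The plan compares bullying between arms at baseline but states no response if the arms differ, and an adjustment added after seeing that comparison would look data-driven.

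**Working it through.** **Inputs from the article.** Control prevalence 3.8%; target reductions 0.8 to 1.9 points; about 4,200 pupils in 20 schools, 1:1, hence 10 schools per arm and 4,200/20 = 210 pupils per school.

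**Assumed, because the article gives no value.** ICC 0.005 to 0.03; two-sided 5% test; baseline-endpoint correlations (true school level / pupil level) of 0.3/0.2, 0.5/0.3 and 0.7/0.4.

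**The plan's own figure.** The stated 388 to 2,148 students reproduces from a one-sample precision formula with finite-population correction: n0 = 1.96²·p(1−p)/d², n = n0/(1 + (n0−1)/100,000), p = 0.038.
- d = 0.019: n0 = 389.0, n = 387.5, rounded up to 388.
- d = 0.008: n0 = 2,194.3, n = 2,147.2, rounded up to 2,148.

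The formula has no power term and does not compare two arms, so it shows no reserve that would make lost precision harmless. That is a separate issue.

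**Chance imbalance at baseline.** SD of the between-arm difference = √[(2/10)·(ICC·pq + (1−ICC)·pq/210)], with pq = 0.038 × 0.962 = 0.03656. At ICC 0.01: √[0.2·(0.000366 + 0.000172)] = 0.0104, or 1.04 points. This takes no account of school type or socio-economic status.

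| ICC | SD (points) | Chance of a gap above 0.8 points |
|---|---|---|
| 0.005 | 0.84 | 34% |
| 0.01 | 1.04 | 44% |
| 0.02 | 1.34 | 55% |
| 0.03 | 1.59 | 62% |

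The SD is at or above the smaller target effect throughout. Against the larger one it is 0.84/1.9 = 0.44 to 1.59/1.9 = 0.84 of the effect.

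**Gain from adjustment, 3.8% versus 1.9%.** With mean prevalence 0.0285, v = 0.0285 × 0.9715 = 0.02769. The school component is sb = ICC·v and the pupil component is sw = (1−ICC)·v/210. Unadjusted variance = (2/10)(sb + sw). Adjusted variance = (2/10)[sb(1−r_school²) + sw(1−r_pupil²)]. Power is from the noncentral t, with 18 df unadjusted and 17 adjusted.

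At ICC 0.01, sb = 0.000277 and sw = 0.000131. The unadjusted SE is √(0.2 × 0.000407) = 0.0090, and power is 51%. With correlations 0.5/0.3 the bracket becomes 0.000208 + 0.000119 = 0.000326, a 20% reduction, and power is 60%.

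| ICC | Unadjusted | 0.3/0.2 | 0.5/0.3 | 0.7/0.4 |
|---|---|---|---|---|
| 0.005 | 69% | 71% | 76% | 85% |
| 0.01 | 51% | 54% | 60% | 72% |
| 0.02 | 34% | 36% | 41% | 53% |
| 0.03 | 26% | 27% | 31% | 41% |

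The variance reductions are 7–8%, 17–23% and 33–45% for the three correlation pairs.

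**A more optimistic version.** If (1−r²) is applied to the whole variance, r is the correlation of observed school prevalences. At ICC 0.01, r = 0.5 gives 63% and r = 0.7 gives about 79%. The reliability of an observed school prevalence is sb/(sb + sw) = 0.68, so r = 0.7 needs, for example, a true school correlation of 0.85 and a pupil correlation of 0.4: 0.85 × 0.68 + 0.4 × 0.32 = 0.71.

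**Smaller target, 3.8% versus 3.0%, ICC 0.01.** Power is 12% unadjusted, 13–17% with the three correlation pairs, and 19% with r = 0.7 on observed prevalences.

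**The case against.** **The list may be condensed.** The Abstract speaks of covariates at school, classroom and student level, yet Planned Analyses names none at classroom level, and a fuller plan may exist. This has some weight: the article never says that baseline is excluded. But it does state an adjustment set, and it marks only the moderator list as open-ended. The point is about a stated model, not a missing detail.

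**The analysis is valid without baseline.** This stands. A reader might infer that the treatment estimate is biased. The documents do not support that: allocation was random, and a school-level random effect carries chance differences between schools into the standard error. The interval already allows for them; it is wider than it needs to be.

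**Imbalance is partly controlled.** Each arm has five primary and five secondary schools, school type and socio-economic status are covariates, and entry required a previous rate of at least 5%. The SDs above ignore this and so overstate the imbalance left in the planned model, by an unknown amount.

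**The gain is assumption-dependent.** This stands. With weak correlations it is one to three power points.

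**Baseline has its own difficulties.** It ran from late January to early February 2019, after allocation, which was not concealed, and the intervention started in February. The earlier Sociescuela rate predates randomization, but may be up to three years old and is truncated at 5%, so it may predict less well. Nor can every pupil be assumed to have a baseline value. These affect how the covariate is built, not whether to use one.

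**Adjustment in a logistic model is not plain variance reduction.** It changes the conditional odds ratio and can widen that ratio's interval. This also stands and is met in the fix.

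**Conclusion.** The point holds as a matter of efficiency and chance imbalance and should be corrected; it does not invalidate the trial's analysis. The stated model leaves out a covariate measured with the same instrument in both arms and all 20 schools.

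Under the assumptions listed, the chance SD of the baseline difference is about 0.8 to 1.6 points before any allowance for school type or socio-economic status. Adjustment would reduce the variance by roughly 7% to 45%. At ICC 0.01, power for the 1.9-point reduction goes from about 51% to 54–72%, approaching 80% only if observed school prevalences correlate at 0.7.

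A reader might also infer that adjustment would bring the trial to its stated 80% power across the target range. It would not: for the 0.8-point reduction, power at ICC 0.01 stays below about 20% in every case examined. Nor should the imbalance be called as large as the effect sought without saying which effect: that holds against 0.8 points, not 1.9.

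**What to change.** In Planned Analyses, add to the primary model:

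- each pupil's baseline peer-reported victimization status, with a missing-indicator for pupils without a baseline value;
- the school's baseline prevalence, or its earlier Sociescuela rate where baseline was collected after the intervention began.

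For the continuous secondary outcomes (SDQ, depressive symptoms, CAPE-P15, Rosenberg, KIDSCREEN-10), add the pupil's baseline score.

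If the primary model is logistic, report the marginal risk difference beside the conditional odds ratio, because the odds ratio changes meaning when baseline is added.

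Make the change before the arms are compared. If the comparison has already been run, report the adjusted analysis and label it as added later.

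The cost is a line or two of text and one or two school-level degrees of freedom. No new data are needed.

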One of the main predictors of being victimized by peers is to be identified as different. Despite intensive efforts to facilitate integration of children with disabilities and special educational or health care needs into mainstream educational systems, they remain at greater risk of both bullying and mental disorders (28–31). In this population, exposure to bullying seems to be a significant mediator between disability and psychosocial stress and mental health (32, 33). For instance, children with autism show a three-fold higher risk of being victimized by peers relative to typically developing individuals (34), and bullying behavior is associated with increased risk of psychological distress, depression, anxiety disorders, and suicidal behavior, as well as poorer educational outcomes in this population (35–41). In fact, one recent longitudinal study found that bullying is a substantial contributor to increased depression rates in young people with autism traits from childhood to adolescence relative to typically developing individuals, even after accounting for genetic risk (42). Some targeted interventions have been developed for children with autism (e.g., peer network interventions, video modeling), and preliminary reports based on very small samples suggest efficacy in reducing peer victimization (43, 44). Some effective parent-assisted social skill training programs for young people with autism, such as the UCLA PEERS Program, also include content that targets bullying, but efficacy on this outcome has not been specifically assessed (45). Despite efforts to achieve a more inclusive educational system (with special needs children mainstreamed into regular schools) and higher bullying rates in these already vulnerable populations, to our knowledge no previous school-based universal prevention program has specifically addressed bullying in youth with special educational needs (SEN) or assessed the efficacy of universal primary preventive anti-bullying interventions in this population.

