#### Students With Special Educational Needs

Additional variables regarding the numbers of pupils with SEN, availability of specific resources for children with neurodevelopmental disorders at each school, and diagnoses for which the pupils receive educational support are collected from the class teachers through the online platform.

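### The outcome models omit SEN status, a recorded risk factor; adding it is a nearly free improvement of low weight, not the repair of a bias

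*Protocol article*

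**What the plan says.** Planned Analyses sets out one model for every outcome: "Multi-level mixed model analyses (three levels: school, classroom, and student) will be performed", "while controlling for school socio-economic status, primary vs. secondary school, sex, and age". That is two school-level covariates (socio-economic status and school type) and two pupil-level covariates (sex and age). The list is closed, whereas the list of possible effect modifiers in the same section is left open-ended.

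SEN appears elsewhere in the protocol article:

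- The Introduction says of children with disabilities and special educational or health care needs that "they remain at greater risk of both bullying and mental disorders". The only risk ratio it gives is for one subgroup: "children with autism show a three-fold higher risk of being victimized by peers".
- School Recruitment requires specialised resources in primary schools: "The latter criterion was used to enrich the sample for children with neurodevelopmental conditions".
- The section on students with SEN says that the number of such pupils and the "diagnoses for which the pupils receive educational support are collected from the class teachers through the online platform".
- Planned Analyses uses SEN twice: to define a subgroup, and, as a school proportion, as a possible modifier within the intervention arm only. Neither use adjusts the comparison between arms.

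The abstract describes the models as "adjusting for school-, classroom-, and student-related covariates".

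**The concern.** A variable that predicts the primary outcome and the mental health outcomes, and that is already collected, would normally be a candidate for pre-specified adjustment. With 10 schools per arm, randomisation can leave the arms with different SEN shares. The plan would not remove that difference from the estimate, and adjusting for it later would be a post hoc choice. Planned Analyses does foresee a baseline comparison of demographic, educational and bullying variables, but it names no response if SEN differs there.

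The abstract raises a smaller point of consistency. It refers to covariates at classroom level, but the models contain classroom only as a level of clustering.

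**Working it through.** The plan gives no figure for SEN imbalance, so there is none to reproduce. The benchmark effects do follow from the Sample Size Calculation: 20% of 3.8% is 0.76, stated as 0.8 points, and 50% of 3.8% is 1.9 points.

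**Inputs from the protocol article**
- Prevalence p = 3.8%.
- 10 schools per arm, 5 primary and 5 secondary.
- About 4,200 pupils in 20 schools, so m = 4,200/20 = 210 per school.
- Risk ratio 3, stated for autism only and used here as an upper value.

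**Assumptions (not in the protocol article)**
- SEN share s = 5-10%.
- Between-school SD of the share = 2-6 points.
- Lower risk ratio = 2.
- ICC = 0.01-0.05.

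**Step 1. Excess risk in SEN pupils.** Hold overall prevalence at 3.8%. The risk without SEN is p0 = 0.038/(1 + s(RR - 1)) and the excess is p0(RR - 1).
- RR 2: 0.038/1.05 = 3.62 points (s = 5%); 0.038/1.10 = 3.45 points (s = 10%).
- RR 3: 2 × 0.038/1.10 = 6.91 points (s = 5%); 2 × 0.038/1.20 = 6.33 points (s = 10%).

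**Step 2. Chance difference in mean SEN share between arms.** Its SD is SD_school × sqrt(2/10) = 0.447 × SD_school. For school SDs of 2, 4 and 6 points this is 0.89, 1.79 and 2.68 points.

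**Step 3. Shift in the prevalence difference for a one-SD imbalance** (step 1 × step 2, in percentage points)

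| RR, SEN share | SD 2 | SD 4 | SD 6 |
|---|---|---|---|
| 2, 5% | 0.03 | 0.06 | 0.10 |
| 2, 10% | 0.03 | 0.06 | 0.09 |
| 3, 5% | 0.06 | 0.12 | 0.19 |
| 3, 10% | 0.06 | 0.11 | 0.17 |

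The range of 0.03-0.19 points is about 4-23% of the 0.8-point effect and 2-10% of the 1.9-point effect.

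**Step 4. Standard error of the crude difference.** SE = sqrt(2p(1 - p)(1 + (m - 1)ICC)/(10m)).
- ICC 0.01: design effect 1 + 209 × 0.01 = 3.09; SE = sqrt(2 × 0.0366 × 3.09/2,100) = 1.04 points.
- ICC 0.05: design effect 11.45; SE = 2.00 points.

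**Step 5. Share of variance.** (shift/SE)² runs from (0.03/2.00)², about 0.02%, to (0.185/1.04)², about 3.2%. Removing 3.2% of the variance shortens the standard error by 1 - sqrt(1 - 0.032) = 1.6%.

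**Step 6. Imbalance needed to mimic the smaller effect.** With s = 5%, the arms would have to differ in mean SEN share by 0.8/0.0691 = 11.6 points (RR 3) or 0.8/0.0362 = 22.1 points (RR 2). Even at a school SD of 6 points, 11.6 points is 11.6/2.68 = 4.3 SDs of the chance difference.

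**The case against.** The strongest reply is that this is a matter of preference. Randomised schools give an unbiased comparison whether or not SEN is in the model. Chance imbalance is part of the between-school variation that the school level carries into the standard error, and the four chosen covariates are defensible. All of this stands, and it is why the point carries little weight. It does not make the omission a good choice, because the variable is prognostic on the protocol's own account and is already needed for each pupil.

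A second reply concerns timing. No section says when teachers record SEN, and schools were not blinded. Status recorded after the intervention began could be influenced by allocation, so adjusting for it would not be harmless. This also stands, and it sets a condition on the fix.

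A reader might infer more than the protocol article supports:

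- *That the estimate is biased.* Randomisation rules out systematic bias from the omission itself. Unconcealed allocation combined with active parental consent could in principle let consent differ by SEN status. The article does not say when consent was sought relative to allocation, and it gives no sign that consent differed, so this remains a possibility only.
- *That imbalance could use up much of the target effect.* Setting a 95% extreme (1.96 × 0.185 = 0.36 points) against the 0.8-point end looks large. But the estimate itself has a 95% margin of at least 1.96 × 1.04 = 2.0 points, which already allows for such chance differences.
- *That SEN explains nearly a tenth of the variance.* This follows only if the ICC is set to zero: SE = sqrt(2 × 0.0366/2,100) = 0.59 points, and (0.185/0.59)² is about 10%. A zero ICC is not a sensible reference for a school-randomised trial.
- *That enrichment makes arm imbalance likely.* The enriching criterion applied to every primary school selected and to no secondary school. Each arm has five of each type, and school type is a covariate. Only variation within school type remains.
- *That all SEN pupils carry a three-fold risk.* The article states that figure for autism alone.

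**Conclusion.** The omission is real and easily corrected, and its consequence is small. It forgoes a precision gain of about 0-3% of the variance of the primary comparison, and a pre-specified answer to a chance imbalance in SEN share within school type. Validity is not at issue.

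The size rests on the assumed SEN share, between-school SD and ICC, on a risk ratio whose upper value is borrowed from autism, and on a crude prevalence difference at 3.8%. The school SD should be read as variation within school type. Covariates already in the model may lower both the standard error and the residual SEN imbalance. For the mental health and quality-of-life outcomes the article gives no size for the association with SEN, so no figure is offered.

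The missing classroom covariate is an editorial mismatch and adds nothing to the case about SEN.

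**What to change.** Add pupil-level SEN status to the covariates of the primary and all secondary outcome models, restricted to status established before the intervention started in February 2019, and state when and by whom it was recorded. Post-intervention data were collected in May-June 2019. If outcomes have already been examined by arm, keep the stated covariates for the main analysis and report the SEN-adjusted model as a dated sensitivity analysis.

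Separately, make the abstract and Planned Analyses agree: either remove the reference to classroom covariates, or name one, for which the class SEN share is available.

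The cost is one model term from data already collected, a check on the date of recording, and a dated change to the analysis wording. No new data are needed and no stated sample size changes.
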